### Sample size calculation

This is a superiority trial in which sample size determination was performed through prior study [45] information based on the primary PADL variable. With the expectation of an increase in the number of steps of 45% (approximately 2260 steps) in the FTG compared with the CTG and UTG (both with no expected increase), using a standard deviation of 2603 steps, and loss at follow-up of 20% of individuals (values commonly found in the study population) [44], 25 individuals will be required in each of the three groups to obtain a power of 80%, adopting an α of 5%.

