### Statistical analysis

The statistical program SPSS 22.0 (IBM, Armonk, NY, USA) will be used. The data will be submitted to the normality test of Kolmogorov–Smirnov, and if they present normal distribution, the descriptive variables will be expressed as mean and standard deviation; if they do not fit the Gaussian distribution model, data will be presented as median and interquartile range. Mauchly’s sphericity test will be performed. Once the sphericity is assumed, two-way analysis of variance (ANOVA) will be performed to evaluate the possible intra- and inter-group differences (FTG, CTG, and UCG) at pre-intervention, post-intervention, and post-*follow-up*. The Tukey post-hoc will be used to identify the specific differences in the variables in which the F values found are higher than the established statistical significance criterion. To evaluate the effect size between interventions, Cohen’s d test will be used. The level of significance adopted will be 5%. Data integrity will be monitored by regularly scrutinizing data files for omissions and errors. Participants will be given an anonymous study ID to protect confidentiality, and only study investigators will have access to the final trial data set.

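### Tukey over all three pairs leaves FTG vs CTG, the comparison the trial is about, with about 63% power (75% at 25 per group) rather than 80%

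*Protocol article*

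**What the plan says.** The Statistical analysis section plans a two-way ANOVA, three groups by three time points, at a 5% level. On pairwise comparisons: "The Tukey post-hoc will be used to identify the specific differences in the variables in which the F values found are higher" than the criterion. It gives no order among the pairs and does not say which F (group, time or interaction) opens the door to them.

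The Sample size calculation section assumes an increase of about 2260 steps "in the FTG compared with the CTG and UTG (both with no expected increase" (UTG is evidently the usual care group), "using a standard deviation of 2603 steps", and "loss at follow-up of 20% of individuals". It concludes that "25 individuals will be required in each of the three groups to obtain a power of 80%, adopting an α of 5" per cent. It does not name the test being powered and mentions no adjustment for three pairs.

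The Introduction gives the aim as the effect of adding the functional circuit to combined aerobic and resistance training, which is FTG vs CTG. The Analysis of the population section fills missing values with the latest assessment, so up to 25 per group may be analysed.

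**The concern.** The test that answers the trial's question is not the test that appears to have been sized. Tukey spreads the 5% over three pairs. One of them, CTG vs UCG, is expected to show nothing ("both with no expected increase") and carries no stated hypothesis. FTG vs CTG bears the cost.

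At stake is the chance of detecting the planned 2260-step benefit with a fixed 75 patients. If that chance is well below 80%, a negative FTG vs CTG result is likely to be over-read, and a change in the testing rule could have recovered much of the shortfall.

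**Working it through.** **Inputs.** Difference 2260 steps, SD 2603, CTG and UCG equal, 25 randomised per group, 20% loss, α 5%: all from the Sample size calculation section. Two-sided testing is assumed, since the text does not say.

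d = 2260 / 2603 = 0.868. Evaluable per group = 25 × 0.8 = 20.

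**1. Reproducing the plan's 80%.**
- Omnibus F for three groups: λ = n × (2/3) × d² = 20 × 0.667 × 0.754 = 10.05, with 2 and 57 df and critical F 3.16. Power is 79.5%, and 20 / 0.8 = 25 per group.
- Unadjusted comparison of two means (normal approximation): 0.868 × √(20/2) = 2.746, and 2.746 − 1.960 = 0.786, so 78.4%. The two-sample t gives 76.3%.

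The stated 25 per group therefore fits the omnibus F, or roughly an unadjusted pairwise test. It does not fit a Tukey comparison.

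**2. Power of FTG vs CTG under the planned rule.** With the pooled three-group variance, power is the noncentral t probability beyond the critical value, with noncentrality d√(n/2).
- n = 20: noncentrality 2.746, 57 df. Unadjusted critical value 2.002; Tukey critical value q/√2 = 2.406.
- n = 25: noncentrality 0.868 × √12.5 = 3.070, 72 df. Critical values 1.993 and 2.393.

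The gated rules were simulated with one million trials per setting:

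| Rule, one time point | 20 per group | 25 per group |
|---|---|---|
| F, then Tukey (plan) | 62.8% | 74.6% |
| Tukey without the F gate | 63.3% | 74.9% |
| (a) three-group F, then unadjusted pairs | 71.8% | 82.4% |
| (b) FTG vs CTG first at 5% | 77.0% | 85.7% |

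Gain at 20 per group: 71.8 − 62.8 = 9.0 points for (a) and 77.0 − 62.8 = 14.2 for (b). At 25 per group: 82.4 − 74.6 = 7.8 and 85.7 − 74.6 = 11.1. The gate itself costs 63.3 − 62.8 = 0.5 point; the rest is the step from 2.002 to 2.406.

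Both FTG contrasts are significant in 48% of trials under the plan, 64% under (a) and 65% under (b), at 20 per group.

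**3. Error control at one time point.** With all means equal, any false pair occurs in 5.0% of trials under (a) and 4.5% under F then Tukey. With two groups equal and the third far away, a false difference between the equal two occurs in 5.0% under (a) and 1.9% under the plan. With three groups, (a) is a closed test: if only one pair is truly equal, only one false rejection is possible, and it is tested at 5%. The fixed sequence in (b) holds 5% by construction.

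**4. Sensitivity to the means (20 per group).**
- UCG midway between FTG and CTG: (a) gives 65.3% against 61.9% for FTG vs CTG, a gain of only 3.4 points.
- UCG 2260 steps below CTG: (a) gives 77.0% against 63.3%.
- CTG midway between FTG and UCG: FTG vs UCG succeeds in about 25% of trials under (b), because FTG vs CTG must succeed first. The figure is 62% under the plan and 65% under (a).

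**5. The planned three-by-three layout.** A mixed-model simulation used the interaction F as gate, a true effect at week 8 only, an assumed within-patient correlation of 0.3 to 0.7, and 20,000 trials per setting. With unadjusted tests at both later visits, a false group difference at follow-up appeared in about 9–12% of trials. With Tukey it was about 4–5%.

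**The case against.** F followed by Tukey is standard and does not inflate error, so nothing in the section is incorrect as statistics. That stands: this is a loss of efficiency and a mismatch with the sizing, not a fault of validity.

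A reader might go further and infer that the plan pays twice for multiplicity, or that Tukey after a significant F protects nothing. The first does not hold, because the gate costs only about half a point. The second is true only for a three-group F at a single time point. The protocol plans a two-way ANOVA with two post-baseline visits and leaves the gating F unnamed. If the interaction F is the gate, Tukey does real work, as step 5 shows. A gain at week 8 that fades by three months is one of the outcomes the trial is designed to look for.

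It can also be said that a full analysis plan might set a testing order. It might, but the article already commits to Tukey after F, and that commitment is what is assessed here. Finally, the gain is not one fixed figure: it shrinks if 25 per group are analysed, and for (a) it nearly vanishes if UCG lies midway.

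**Conclusion.** The point holds as a matter of efficiency. On the protocol's own assumptions FTG vs CTG has about 63% power at 20 evaluable per group, not 80%. It has about 75% if carry-forward keeps 25; that figure is generous, since it supposes carried-forward values show the same mean difference and SD as observed ones. A better-aimed rule recovers 9–14 points at 20 per group and 8–11 at 25 with family-wise error still at 5%, but only about 3 points for (a) if UCG lies midway between FTG and CTG.

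The figures rest on two-sided tests, equal variances, an SD of 2603 that applies to the quantity analysed, and one time point. A reader might conclude that the 80% is an arithmetical error. The document does not support that: the figure reproduces for the omnibus F, but that is not the test that answers the question.

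**What to change.** In the Statistical analysis section, for the primary endpoint, name one measure (for example steps, since the Primary outcome section lists both steps and time in activities) and one time point (for example week 8). Then choose one of two rules there:

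- **(a)** a three-group F at that time point and, if significant at 5%, unadjusted pairwise tests; or
- **(b)** FTG vs CTG first at two-sided 5%, then FTG vs UCG at 5% only if the first is significant, with CTG vs UCG reported as an estimate with its confidence interval.

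Do not replace Tukey with unadjusted tests after the three-by-three interaction F at both later visits.

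The cost is a short rewording before the data are examined, with no extra patients. Rule (b) has a further price: CTG vs UCG is no longer confirmatory, and FTG vs UCG cannot be claimed if FTG vs CTG fails. Rule (a) has neither drawback but gains less. If Tukey is kept, the sample size section should give the power for FTG vs CTG under Tukey.

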## Discussion

### Potential impact and significance of the study

The present proposal was developed through extensive literature research on this topic. Through the interpretation of the results found in several studies, it was possible to develop this concise and structured training protocol. The use of this protocol in the treatment of COPD will confirm whether the addition of functional physical training to a conventional training will promote positive effects on PADL and functionality and whether there will be maintenance of possible gains at the 3-month post-training follow-up.

### Strengths and limitations of the study

This study presents as a strong point the follow-up 3 months after training as this allows evaluation of whether the possible changes resulting from the protocol will be maintained. The assessment of PADL via accelerometers as primary outcome is a strong point as it is an objective measurement and does not suffer influence of personnel involved in the study. Another strong point that can be considered is the fact of this being a randomized clinical trial, which makes the study more reliable. The fact that the study is performed in only one center is considered a limitation, as is the inability to blind the therapists and patients to the training protocol.

### Contribution and clinical applicability

The results obtained in the proposed protocol may provide subsidies via publication for the implementation and insertion of a physical training circuit in the rehabilitation of patients with COPD. In addition, the proposed functional exercises are easily applicable and simulate ADLs not requiring specific equipment and therefore can be implemented in several PR centers.

### Trial status

Protocol number: RBR-3zmh3r. Recruiting: Study start date: March 7, 2018. Study completion date: December 2019.

## Data Availability

Not applicable.

## Abbreviations

1RM: 1-repetition maximum
6MWT: 6-minute walk test
ADLs: Activities of daily living
ATS: American Thoracic Society
COPD: Chronic obstructive pulmonary disease
CTG: Conventional training group
FCT/UNESP: Universidade Estadual Paulista
FTG: Functional circuit training group
LCADL: London Chest Activity of Daily Living
PADL: Physical activity in daily life
PR: Pulmonary rehabilitation
UCG: Usual care group
